**3.e "Transmission fitness" of HIV-1 drug resistance**

Overall, the transmission dynamics of HIV-1 drug resistance mutations remains poorly understood, both at the individual level (between partner-pairs) and among HIV-infected populations. At the individual level, it is still unclear whether HIV-1 drug resistance mutations reduce "transmission fitness", the relative ability of a virus to infect a susceptible host. Using an *in vitro* assay, one study found that MDR HIV-1 was, in fact, more infectious than wild-type virus [113], although the viruses that were studied did not have the decreased RC that is typically associated with multi-drug resistance [114, 115]. Greater RC has been correlated with increased risk of transmission in an experimental model of vaginal transmission of simian immunodeficiency virus [116] and in analysis of mother-to-child transmission [117]. Prediction models for population-level transmission dynamics of HIV-1 drug resistance must be complex, because there is wide variability in RC for any given mutation [118], even between the virus transmitted from source to recipient partners [39], *and host factors likely play a significant role in the clinical progression of disease and risks for subsequent HIV-1 transmission [119]*.

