**3.g Summary**

Although results from many previous studies have increased our understanding of the prevalence and impact of transmitted HIV-1 drug resistance among HIV-infected individuals, most of these studies have been limited by their use of consensus sequencing, and many questions relevant to clinical and public health remain unanswered. Public health surveillance programs would benefit from more accurate estimates of the prevalence of transmitted HIV-1 drug resistance, as would clinicians who recommend empiric ARV therapy without the benefit of resistance testing results for individuals with acute HIV-1 infection or in cases of post-exposure prophylaxis. Studies are needed to understand whether there are differences in the time to loss of detection of HIV-1 drug resistance mutations that are detected by consensus sequencing and by more-sensitive methods in order to guide recommendations for the timing of HIV-1 drug resistance testing. If transmitted low-frequency HIV-1 drug resistance mutations are rapidly lost to detection following HIV-1 acquisition, consideration should be made as to whether resistance testing should be routinely incorporated into HIV-1 confirmatory testing and public health surveillance (*i.e. prior to entry into clinical care*), especially in areas where recent infections *and public health-based HIV testing account for* a large proportion of new HIV-1 diagnoses. Studies are needed to assess the impact of low-frequency HIV-1 drug resistance mutations on disease progression and response to ARV therapy to determine whether the routine use of more-sensitive resistance assays should be considered for future study and widespread use. Further understanding of the factors associated with the dynamics of HIV-1 drug resistance during ARV therapy is needed to help clinicians to make decisions about the timing and potency of ARV treatment regimens. Finally, "transmission fitness" is a concept that is poorly understood, and additional data is needed to determine whether transmitted HIV-1 drug resistance impacts the risk of HIV-1 transmission at both the individual and population level. The studies described in this application have been specifically designed to answer these and other important questions.

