**5. Research Design and Methods**

**5.a Overview of study design and rationale**

The studies proposed in this section will provide a better understanding of the prevalence and dynamics of low-frequency HIV-1 drug resistance mutations in ARV-naïve subjects during primary HIV-1 infection (**Aim #1**), the impact of low-frequency drug resistance mutations on response to ARV therapy (**Aim #2**), and the relative "transmission fitness" of mutant viruses (**Aim #3**). The project will be powered to perform the longitudinal analyses described in the first two studies with use of samples from *approximately 100* subjects who previously enrolled in the PIC Cohort study within 30 days after HIV-1 infection and from *80* subjects who will be enrolled prospectively. Eligibility will be restricted to subjects who acquired HIV-1 infection after 1996, when highly active ARV therapy became widely available in Seattle. OLA will be used to evaluate HIV-1 drug resistance in the PBMCs, blood and seminal plasma from ARV-naïve PIC subjects at baseline (the first available specimen), and 6 and 12 months after HIV infection (**Aim #1)** and in PBMCs 6 and 12 months after the start of ARV therapy (**Aim #2)** to detect changes in the levels of low-frequency HIV-1 drug resistance over time.

The third aim will study PIC subjects and their source partners enrolled in the PIC Cohort and PIC Partners studies. After the transmission relationships are confirmed by molecular methods, this cross-sectional analysis will compare the results of HIV-1 drug resistance testing performed on PBMCs and blood plasma from PIC subjects with the results of resistance testing performed on PBMCs, blood plasma, and genital secretions from their confirmed source partners. The partner-pairs studied in this third aim will also include retrospective analysis of previously collected specimens and continued prospective enrollment in order to maximize the precision of estimates of "transmission fitness" to be described in **5.c.3 Aim #3**.

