**5.c.3 Aim #3: Compare HIV-1 drug resistance patterns in PIC subjects and their source partners.**

This cross-sectional study will evaluate the prevalence and patterns of HIV-1 drug resistance in partner-pairs and compare results of HIV-1 drug resistance testing in the PBMCs, blood plasma, and genital secretions (when available) from the confirmed source partner with test results in PBMCs and blood plasma from the recipient partner. We hypothesize that HIV-1 drug resistant variants will have lower "transmission fitness" compared to wild-type variants, and drug resistance will occur less frequently and at lower levels in the PBMCs and plasma from PIC subjects than in the PBMCs, blood plasma, and genital secretions from their confirmed source partners. Because the most common risk for HIV-1 acquisition reported among our cohort is receptive anal intercourse, the ideal comparison would evaluate the results of HIV-1 drug resistance testing in semen specimens from every source partner. However, not all potential source partners collect genital secretions for study. As previous studies have shown that there is moderate concordance between HIV-1 drug resistance testing results in blood and semen [61-63], our proposed comparison using the results of resistance testing in the blood of source partners should have relevance.

For every subject enrolled in the PIC Cohort study, we will attempt to identify and study all source partners through the methods described below in **5.d.2 PIC Partners study** and **5.e Laboratory methods**.If OLA is not performed as part of the other studies previously described in this application, OLA will be performed on the first available PBMC and plasma specimens from PIC enrollees and on the PBMC, blood plasma, and genital secretions from confirmed source partners. We hypothesize that many but not all mutations in the source partner will be identified in the recipient partner and that low-frequency mutations detected in the recipient partner will be present at lower levels compared to their levels in the source partners. Secondary analyses will explore whether the probability of transmission differs between specific HIV-1 drug resistance mutations.

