Analysis for the primary objective will be calculated as a binomial probability of the number of mutations transmitted from each source partner to the recipient partner, conditional on the number of mutations in the source partner. This accounts for the fact that source partners will undoubtedly have different numbers of HIV-1 drug resistance mutations. For the purpose of sample size calculations, we assume that the number of mutations in the source partners follows a Poisson distribution with the expected number of mutations being two. Power calculations are based on simulations, repeated 1000 times. Each simulation estimates the binomial probability of transmitting a mutation conditional on the number of mutations in the source partners, and calculates the associated 95% confidence intervals based on normal approximation for the estimated probability. The type II error is calculated as the number of simulation replicates where the 95% confidence interval contains the value of 1, when the simulated transmission probability is less than 1.

Using the simulation analyses described above, we will have 82% power to detect a transmission probability of all source partner mutations of 80% or less if we have 17 confirmed partner-pairs in which the source partner has at least one HIV-1 drug resistance mutation. *Overall, the subset of recipient partners who had resistance identified by OLA (4/12=33%) was similar to the population studied in the pilot project. Of the 18 confirmed partner pairs without complete OLA testing, we would expect 6 to 18 source partners to have HIV-1 drug resistance. Based on our prior experience with confirming putative source partners, we would expect that the relationship of 14 of the remaining 17 partner-pairs would be confirmed, and 5 to 17 of these source partners would have HIV-1 drug resistance. We would therefore need to enroll at most 21 (and likely fewer) new putative source partners in order to have at least 6 additional confirmed source partners with HIV-1 drug resistance.*

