**Figure 6: Methods for recruitment and identification of transmitting (source) partners for PIC Partners study**

PIC enrollee presents with primary HIV-1 infection, is eligible, and consents to PIC Cohort study.

PIC enrollee identifies all partners with whom s/he had contact in the 3 months prior to the estimated date of HIV-1 acquisition.

Potential source partner is notified by PIC enrollee or by PIC staff and consents to PIC Partners study.

PIC Partner is found to be infected with HIV-1, and viral sequences of PIC enrollee and Partner show high degree of homology.

When available, we will use stored samples for Aim #3 from subjects who previously enrolled in the PIC Partners study. We will also continue to identify putative source partners of new subjects enrolled into the PIC Cohort study. Persons will be eligible for screening if they are at least 18 years old and were identified by the PIC enrollee to be a sex partner or needle-sharing partner in the three months prior to the PIC enrollee's estimated date of HIV-1 acquisition. Enrollees can refer partners or have referral orchestrated by PIC clinicians. If referral is performed by PIC staff, partner notification follows procedures outlined in the Washington State HIV Partner Notification Guide, and the identity of the PIC enrollee is not revealed to the potential source partner. Contact with all eligible partners of PIC enrollees will be attempted, and the schedule of evaluations (**Table 12**) will be similar to the current PIC Partners schedule of evaluations. Blood and other specimens not utilized for the aims detailed in this application will be stored to be available for future immunologic and virologic investigations.

**Table 12: PIC Partners study schedule o**f evaluations

|  | Visit #1  Screening | Visit #2  Entry |
| --- | --- | --- |
| Informed Consent | X |  |
| Screening Questionnaire | X |  |
| HIV-1 testing (antibody, LS-EIA, Western blot, & plasma HIV-1 RNA) | X |  |
| Vital signs/weight |  | X |
| History and Physical Exam |  | X |
| CD4+ T-cell count/subsets |  | X |
| Immunology panel (HLA typing, CTL assays) |  | X1 |
| Serum storage |  | X1 |
| Plasma/PBMCs storage |  | X1 |
| Genital secretions |  | X2,3 |
| *STI screening4* |  | *X* |
| Blood volume (mL) | 15.5 | 111 |
| Length of visit (min) | 60 | 60 |

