**Figure 7: Capture of biotinylated**

**probes on the ELISA plate [1]**

*F*-AC-ATC-CCG-CAG-GGT-TAA-AAA-AAG**-AAC - AAA**-TCA-GTA-ACA-GTA-CTG-GAT-GTG-GGT -*Biotin*

…TG-TAG-GGC-GTC-CCA-ATT-TTT- TTC- TTG - TTT -AGT-CAT- TGT-CAT-GAC-CTA-CAC-CCA…

The ligation products are then captured onto a streptavidin-coated ELISA plate (**Figure 7**), and alkaline phosphatase (AP) labeled anti-fluorescein antibodies and horseradish peroxidase (POD) labeled anti-digoxigenin antibodies are added sequentially. The AP (magenta) and POD (yellow) labeling is quantified by optical density (O.D.) using an ELISA plate reader. In the example above, only mutant virus (magenta) would be detected; however, mixtures of both wild type and mutant viruses are detectable by OLA. Indeterminate reactions occur 2-7% of the time and are typically a result of failure of the ligation reaction due to polymorphisms usually occurring at or adjacent to the two bases to either side of the ligation site. Under those circumstances, no color is produced.

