**5.h.4 Public health surveillance and mathematical modeling**

Estimates of the transmission probabilities of HIV-1 drug resistance obtained in Aim #3 of this project will be used in mathematical models currently being planned through ongoing collaborations within PHSKC and the UW Center for AIDS and STD. Coupled with PHSKC surveillance efforts, these mathematical models will increase our understanding of the population-level dynamics of transmitted HIV-1 drug resistance and will be instrumental to develop public health interventions to reduce the spread of transmitted HIV-1 drug resistance.

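### Aim 3's pooled binomial estimates whether a source mutation is detected in the recipient given infection; judged against 1, it can mask or mimic a loss of transmission fitness, and it is not a risk of transmission

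*Protocol*

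**What the plan says.** Section 3.e defines transmission fitness as "the relative ability of a virus to infect a susceptible host". Section 5.c.3 makes it the Aim 3 hypothesis: "We hypothesize that HIV-1 drug resistant variants will have lower 'transmission fitness' compared to wild-type variants". Section 3.g adds that data are needed on whether resistance "impacts the risk of HIV-1 transmission at both the individual and population level", and says the studies were designed to answer such questions.

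The sampling starts from an infected person. In Figure 6 the first step is "PIC enrollee presents with primary HIV-1 infection, is eligible, and consents to PIC Cohort study", and the partner is then sought. Section 5.a restricts the analysis to proven pairs: "After the transmission relationships are confirmed by molecular methods, this cross-sectional analysis will compare the results of HIV-1 drug resistance testing".

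The primary analysis in 5.c.3 is "a binomial probability of the number of mutations transmitted from each source partner to the recipient partner", conditional on how many mutations the source has. The power simulation counts a replicate as a failure when the normal-approximation 95% interval includes 1. There is no term for the mutant's share of the source's virus. Source and recipient levels are compared only as a secondary objective, with 50-100% as a single category.

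Section 5.h.4 states the use: "Estimates of the transmission probabilities of HIV-1 drug resistance obtained in Aim #3 of this project will be used in mathematical models". Section 5.f lists limitations but does not mention that every pair studied is one in which transmission occurred.

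**The concern.** Relative ability to infect can be seen in this design only where mutant and wild-type virus were both available to be transmitted. If the source carried no wild-type virus at transmission, whatever founded the recipient's infection was mutant, at any relative fitness. A fitness cost in such a source appears as infections that did not happen, and those never enter the sample. These mutations contribute values at or near 1 that say nothing about fitness.

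Mixtures have the opposite problem. A neutral variant making up a minority of the source's virus can be missed by chance at the transmission bottleneck, so 1 is not its expected value under no fitness cost. Excluding 1 is then not evidence of reduced fitness.

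The pooled figure therefore depends on the mix of fixed and mixed mutations and on their levels, as well as on fitness. At stake are the conclusion of Aim 3's only primary objective and the meaning of the number handed to the population models.

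**Working it through.** **Inputs from 5.c.3:** 17 pairs whose source has at least one mutation; source counts Poisson with mean 2; transmission probability 0.80; normal-approximation 95% interval; success if it excludes 1; stated power 82%. Expected mutations in 17 such pairs: 17 × 2/(1 − e⁻²) = 17 × 2.313 ≈ 39.

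**Assumptions (not in the protocol, so varied):** F, the share of source mutations that are fixed; s, the mutant share in a mixed source; w, relative fitness (1 = neutral); k, the number of founder viruses.

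**1. The plan's figure.** Simulation with 20,000 replicates gives 82.0% using the mean of per-pair proportions, with zeros allowed in the Poisson draw. The 82% is therefore reproducible. The pooled binomial with at least one mutation per source gives 95.7%. The issue is what is estimated, not this arithmetic.

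**2. Model.** With one founder, P = ws/(ws + 1 − s). At s = 1, P = w/w = 1 for every w. With k founders, detection is t = 1 − (1 − P)^k. The pooled expectation is F + (1 − F)t.

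**3. Masking.** Let mixed mutations be detected with t = 0.80, the plan's own alternative (pooled test, 17 pairs, at least one mutation each):

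| F | Pooled expectation | Chance interval excludes 1 |
|---|---|---|
| 0 | 0.80 | 96% |
| 0.25 | 0.85 | 85% |
| 0.50 | 0.90 | 56% |
| 0.75 | 0.95 | 14% |
| 0.90 | 0.98 | 1% |
| 1 | 1.00 | 0% |

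With t = 0.50 the chance is 99% at F = 0.50, 72% at 0.75 and 13% at 0.90. Masking is marked only when the fixed share is high or the effect in mixtures is modest.

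**4. Mimicking.** Take w = 1 (no fitness loss) and one founder, so t = s:

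| s | F | Pooled expectation | Chance interval excludes 1 |
|---|---|---|---|
| 0.30 | 0.50 | 0.65 | about 100% |
| 0.30 | 0.75 | 0.825 | 92% |
| 0.30 | 0.90 | 0.93 | 29% |
| 0.50 | 0.50 | 0.75 | 99% |
| 0.50 | 0.90 | 0.95 | 14% |

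**5. Neutral against halved fitness.** With s = 0.30 and one founder, t = 0.30 at w = 1. At w = 0.5, t = 0.15/(0.15 + 0.70) = 0.176. Upper 95% limits for 39 mutations are in brackets:

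| F | w = 1 | w = 0.5 | Difference |
|---|---|---|---|
| 0 | 0.30 (0.44) | 0.18 (0.30) | 0.12 |
| 0.25 | 0.48 (0.63) | 0.38 (0.53) | 0.09 |
| 0.50 | 0.65 (0.80) | 0.59 (0.74) | 0.06 |
| 0.75 | 0.83 (0.94) | 0.79 (0.92) | 0.03 |
| 1 | 1.00 | 1.00 | 0 |

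Except when all mutations are fixed, both columns exclude 1, so the criterion does not separate a neutral variant from one of half fitness. Half-widths for F = 0.25 to 0.75 are about 0.12 to 0.16.

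**6. More founders, F = 0.25.** For k = 2, t = 1 − 0.70² = 0.51 against 1 − 0.824² = 0.32, so the pooled values are 0.63 and 0.49, a difference of 0.14. For k = 3, t = 0.66 against 0.44, and the pooled values are 0.74 and 0.58, a difference of 0.16. The blurring is weaker with several founders, which 3.c considers common.

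**The case against.** **The conditioning is open, and concordance is useful.** Aim 3 refers to confirmed source partners throughout. Its operational hypothesis, that resistance is rarer and at lower levels in recipients than in their sources, can be examined in pairs. This stands as a defence of collecting the data. It does not turn the pooled figure into relative fitness or risk.

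**Levels are already compared.** They are, but as a secondary objective that leaves the primary estimate unchanged, and the 50-100% category merges fixed with majority-mixed mutations.

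**A reader might infer that pooling generally hides a fitness loss and would report it as near-complete transmission.** The figures do not support that. At half fitness the pooled value in step 5 is 0.18 to 0.79 unless everything is fixed, and the error also runs the other way. The pilot hints that the fixed share may be low: among 34 resistant recipients, 28 (82%) had only low-frequency mutations. They are recipients and not sources, so this is suggestive only.

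**A reader might infer that a fixed mutation must be found in the recipient.** That holds for the founder virus only. Later reversion or overgrowth, change in the source before sampling, and indeterminate OLA results (2-7% in 5.e.5; scored negative in the pilot tables) can make it look lost. None of these is transmission fitness. The exploratory adjustment for time since transmission addresses loss of detection, not conditioning on infection.

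**A reader might infer that the models will use the estimate as a per-exposure risk.** Section 5.h.4 does not say so. A probability conditional on infection is a legitimate input if it is labelled as one.

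**Conclusion.** The point holds in this form: the primary estimate of Aim 3 is the probability of detecting a source mutation in the recipient given infection. It is neither transmission fitness relative to wild-type nor a risk of transmission. Judged against 1, it can mask a fitness cost (power 96% falling to 56% at half fixed and 14% at three quarters, with t = 0.80). It can also mimic one: the interval excludes 1 in 92% to about 100% of neutral scenarios with s = 0.30, one founder and F of 0.50 to 0.75.

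The logical part needs no assumed figure, because conditioning on infection and the absence of source level from the primary analysis are both explicit. The sizes rest on assumed fixed shares, source levels and founder numbers. They are ranges and not predictions, and neither direction of error can be called the general result.

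**What to change.** In 5.c.3, keep the pooled figure but call it the *probability that a source mutation is detected in the recipient, given infection*. State that an interval excluding 1 is not read as reduced transmission fitness.

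Report source mutations that OLA reads as mutant only separately, as concordance. Base any statement on transmission fitness on mutations that OLA reads as mixtures with wild-type, with source level as a covariate. Compare these with the detection expected of a neutral variant at that level and not with 1, and state the number of founders as an assumption with a range. The assay already supports the split: 5.e.5 notes that "mixtures of both wild type and mutant viruses are detectable by OLA", and Table 3 reports mutant and mixture separately.

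In 3.g and 5.h.4, state that the estimate is conditional on infection and is not to be entered in models as a risk of transmission.

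The cost is analysis and wording only, with no new specimens or assays. The price is precision. If half of about 39 mutations are mixtures, roughly 20 remain, and the half-width at 0.80 rises from 1.96√(0.16/39) = 0.13 to 1.96√(0.16/20) = 0.18. In the step 5 example, 20 mixtures at 0.30 and 0.18 have half-widths of about 0.20 and 0.17, so halved fitness would still not be resolved. The fitness estimate should be presented as imprecise.

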**3.f Oligonucleotide ligation assay (OLA)**

The range of studies proposed in this application have not previously been conducted using drug resistance assays that were able to detect viral variants comprising less than 10-50% of the viral population [11-16]. Examples of these more-sensitive assays include single genome sequencing [34, 143], primer-specific PCR [16], a ligation-amplification assay [144], and parallel allele-specific sequencing [16]. OLA was developed by [name] and has several advantages over the other more-sensitive assays (**Table 0**).

